### Sample size {14}

A historical retrospective cohort included 44 patients with REP who were indicated for adjuvant chemoradiotherapy (Arm Ahist). The median PFS in this cohort was 4.9 months. Assuming that the time distribution in the Experimental Arm follows a proportional hazard model, a significance level of 5%, and a power of 80%, 65 events are needed to detect a hazard ratio of 1.65 (i.e., median PFS in the Experimental Arm of 8 months). With an assumed recruitment of 38 months and a follow-up duration of six months, 67 patients are needed based on the historical cohort. With the expected screening failure rate of 5% and a dropout rate of 5%, approximately 75 patients with confirmed REP should be enrolled.

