## Statistical methods

### Statistical methods for primary and secondary outcomes {20a}

All data will be described for each arm separately and for the entire group of patients. The appropriate descriptive statistics will be used, i.e., counts and percentages for categorical characteristics and median and interquartile range (IQR) or mean and standard deviation (SD) for continuous characteristics. Depending on the data type, common statistical tests such as Fisher's exact test or chi-square test for comparing categorical variables and nonparametric Mann‒Whitney test or Kruskal‒Wallis test for comparing continuous variables or their parametric alternatives if the assumption of data normality is met will be used for comparison of patient characteristics between arms.

The survival parameters that will be considered are progression-free survival (PFS) and overall survival (OS). PFS is considered the time from the start of radiotherapy to the occurrence of progression or death. OS is considered the time from surgery to death (in relation to GBM). The Kaplan‒Meier method will be used to estimate the probability of survival. Survival comparisons between groups will be made using the log-rank or Gehan-Wilcoxon test. The Cox proportional hazards model will be used to calculate the hazard ratio in univariable and multivariable analyses.

All statistical tests and confidence intervals will be calculated at a significance level of 5%.

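### On the ordinary two-sided 5% reading, 65 experimental events against a historical arm fixed at 44 patients give about 71–73% power, not 80%; the protocol says neither what the 65 events count nor whether the test is one- or two-sided

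*Protocol article*

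**What the plan says.** Sample size {14} of the protocol article describes the comparator as follows: "A historical retrospective cohort included 44 patients with REP who were indicated for adjuvant chemoradiotherapy (Arm Ahist"). It continues: "The median PFS in this cohort was 4.9 months". The design parameters are "a significance level of 5%, and a power of 80" per cent, and the result is that "65 events are needed to detect a hazard ratio of 1.65", explained as "i.e., median PFS in the Experimental Arm of 8 months". Patient numbers follow: "With an assumed recruitment of 38 months and a follow-up duration of six months, 67 patients are needed based on the historical cohort". Allowances for screening failure and dropout bring this to about 75 enrolled.

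Statistical methods {20a} adds: "All statistical tests and confidence intervals will be calculated at a significance level of 5" per cent. It names the log-rank or Gehan-Wilcoxon test for comparing groups. Outcomes {12} makes PFS in the experimental arm versus the historical arm the primary outcome, and Trial design {8} calls the setting confirmatory against that cohort.

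Neither section states whether the test is one- or two-sided. Neither says whether the 65 events are a total, a per-arm figure or the experimental arm alone, or how many of the 44 historical patients had a PFS event.

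**The concern.** The precision of a two-group log-rank comparison depends on the events in both arms. Here one arm is closed: its event count cannot exceed 44 however long the trial runs. A power statement for this design has to carry that limit. The number 65 also happens to be what each arm would need in an equal-arm, two-sided design, and the historical cohort cannot supply 65 events.

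This is the only power statement for the primary endpoint of a trial that calls itself confirmatory. If the test is two-sided, a true improvement from 4.9 to 8 months would be missed in about 27–29% of trials rather than 20%, and a null result would look like stronger evidence against PET-guided planning than the design can give. Unstated sidedness also leaves room to settle the question after the data are seen.

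**Working it through.** **Inputs (Sample size {14}).** Historical arm 44 patients, so at most 44 events. The actual number is not given, and I assume a range of 40 to 44. Medians are 4.9 and 8 months, level 5%, power 80%, stated events 65, stated hazard ratio 1.65 (control over experimental). The medians imply 8/4.9 = 1.633, so both values are carried through. Normal quantiles: 1.960 (two-sided 5%), 1.645 (one-sided 5%), 0.842 (80% power).

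**Step 1: where 65 can come from.**

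- *Equal arms, two-sided 5%.* Schoenfeld: total events = 4(1.960 + 0.842)² / (ln HR)². At 1.633 this is 130.7, or 65.3 per arm; at 1.65 it is 125.2, or 62.6 per arm. Freedman: total = (1.960 + 0.842)² × [(HR + 1)/(HR − 1)]². At 1.65 this is 130.5, or 65.2 per arm.
- *Fixed historical arm, one-sided 5%.* 1/d_exp = (ln HR)² / (1.645 + 0.842)² − 1/d_hist. At 1.633, d_exp is 62.0, 64.1 and 72.1 for 44, 43 and 40 historical events. At 1.65 it is 56.1 with 44 and 64.3 with 40. The range is therefore about 56 to 72.

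Both routes reach 65. The article does not say which was used.

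**Step 2: power of the design as described.** Power = Φ( ln HR / √(1/d_exp + 1/d_hist) − z ). For 65 and 44 events the square root is √(1/65 + 1/44) = 0.1952.

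- HR 1.633, two-sided: 0.4902/0.1952 − 1.960 = 0.551, power 70.9%.
- HR 1.65, two-sided: 0.5008/0.1952 − 1.960 = 0.605, power 72.7%.

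| Experimental + historical events | Two-sided 5%, HR 1.633 / 1.65 | One-sided 5%, HR 1.633 / 1.65 |
|---|---|---|
| 65 + 44 | 70.9% / 72.7% | 80.7% / 82.1% |
| 65 + 40 | 68.4% / 70.3% | 78.7% / 80.2% |
| 55 + 44 | 67.9% / 69.7% | 78.2% / 79.7% |

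A log-rank simulation (20,000 runs, exponential times, 44 versus 65 events, no censoring) agrees: 70.1% and 72.1% two-sided, 80.6% and 81.7% one-sided.

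**Step 3: could 65 be the total over both arms?** With 44 historical events that leaves 21 experimental ones. √(1/21 + 1/44) = 0.2652, and two-sided power is 46–47%. Even an even split of 65 gives only 51–52%. The experimental-arm reading is the only one close to the claim.

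**Step 4: what the design can detect.** With 65 + 44 events, two-sided, the hazard ratio detectable with 80% power is exp(2.802 × 0.1952) = 1.73, a median of 4.9 × 1.73 = 8.5 months. Two-sided 80% power at the planned effect would need 1/d_exp = (ln HR)² / 2.802² − 1/44, that is 127 experimental events at 1.633 or 109 at 1.65.

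**Step 5, separate: events expected from 67 patients.** Assume uniform entry over 38 months, exponential times with median 8 months (rate λ = ln 2/8) and analysis at 44 months. P(event) = 1 − (e^(−6λ) − e^(−44λ)) / (38λ) = 0.826, so 67 × 0.826 ≈ 55 events. The last table row uses this figure.

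**The case against.** The strongest reply is that the section may describe a correct calculation. It opens with the 44-patient cohort and ties the 67 patients to it, which reads naturally as a fixed-control computation. A one-sided 5% test then needs 64.1 experimental events with 43 historical events (HR 1.633) or 64.3 with 40 (HR 1.65), and both round up to 65. The 67 patients would fit as well: if 43 of 44 had progressed, 65 / (43/44) = 66.5. Not all 44 need to have progressed for one-sided power to be about 80%. The article condenses a full protocol in which the sidedness may be stated.

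Much of this stands. A reader might infer that the sponsor took the per-arm number of an equal-arm design and overlooked the size of the historical cohort. The documents do not support that as a fact: they mention no equal arms, and the Schoenfeld match needs 1.633 in place of the printed 1.65 (only Freedman reaches 65 at 1.65). It is likewise too strong to say that the 80% is wrong under every reading.

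What does not stand is that the text can be left alone. Statistical methods {20a} puts all tests and confidence intervals at one 5% level, which is ordinarily read as two-sided tests with 95% intervals, and nothing declares a one-sided test. On that reading the printed power is not that of the printed design. The 55-event figure is a separate matter and depends on its assumptions: the participant timeline follows patients until progression, so a later analysis would collect more events.

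**Conclusion.** The concern holds in conditional form. With a two-sided 5% log-rank test, 65 experimental and 44 historical events, power is 70.9% (HR 1.633) to 72.7% (HR 1.65), against 80% claimed; with 40 historical events it is 68–70%. With a one-sided 5% test it is about 79–82%, in line with the claim. Two-sided is the natural reading of the article but is not stated.

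These figures assume proportional hazards, as the plan does, and that the 65 events all arise in the experimental arm. If the analysis takes place at 44 months with about 55 events, power against 44 historical events is 68–70% two-sided or 78–80% one-sided, under uniform accrual and exponential times. The origin of the number 65 remains open, and the finding does not depend on it.

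**What to change.** In Sample size {14}:

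- state that the 65 events are in the experimental arm;
- give the number of PFS events among the 44 historical patients;
- state the sidedness of the test;
- use 8/4.9 = 1.63 in place of 1.65;
- restate the power for the comparison with the fixed historical arm. If two-sided 5% and all 44 had events: about 71% with 65 experimental events and about 68% with 55, with a detectable hazard ratio of about 1.73 at 80% power with 65 events.

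If the full protocol prespecified a one-sided 5% test, say so both there and in Statistical methods {20a}, report the matching 90% confidence interval, and give the one-sided power: about 81% with 65 events and about 78% with 55, at HR 1.63 with 44 historical events.

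The cost is wording only, with no added patients. The downside is a less favourable stated power, or, on the one-sided route, an explicit commitment to a one-sided test.

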## Methods: participants, interventions, and outcomes

### Study setting {9}

The GlioMET study is a monocentric study. The recruitment period began in October 2020. Patient recruitment in the Czech Republic is planned to be completed in February 2024.

Masaryk Memorial Cancer Institute in the Czech Republic, the coordinating centre for the study, is responsible for educating and training research staff, tracking participants’ enrolment, mathematical analysis, monitoring, pharmacovigilance, data management, and reporting of the study. The control cohort consisted of a historical group of patients collected in the period 2014–2018. Data are collected only from the Czech Republic.

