
### Participant timeline {13}

The schedule of enrolment, intervention and visits is summarized in Tables 1 and 2. The duration of the study participation is 44 months (recruitment 38 months + 6 months follow-up).

**Table 1 Tab1:** Participant timeline for the regimen according to Stupp

4.3.1.Stupp regimen	Screening	CHEMO RADIO THERAPY	Visit 1	Visit 2	Visit 3	Visit 4	Visit 5	Visit 6	Visit 7	Visit 8	Visit 9	Visit 10	Visit 11	Visit 12 (EoT)	Follow-up until PD	EoS Visit
Days / Months	**max. 14 D**	**D1-D42** **(M 1–2)**	**D42 + 1 M** (± 1 tweek)	** + 1 M**	** + 1 M**	** + 1 M**	** + 1 M**	** + 1 M**	** + 1 M**	** + 1 M**	** + 1 M**	** + 1 M**	** + 1 M**	** + 1 M**	**Every 3 M** (± 1 tweek)	**PD**
Inclusion/exclusion criteria	X															
Informed consent	X															
Anamnesis^a^	X															
Pregnancy test (serum/urine)	x*	xx*	x	x	x	x	X	x	x	x	x	x	x			
HIV, HBV, HCV test	X**															
Physical and laboratory examination^b^	X**	x***	x	x	x	x	x	x	x	x	x	x	x	x		
ECOG Performance status	X	x	x	x	x	x	x	x	x	x	x	x	x	x		
Extent of surgery^c^	x															
^11^C-MET PET/CT^d^	x															
Quality of life questionnaires^e^	x			x		x		x		x		x		x	x	
MR and RANO evaluation^f^				x (á 3 months)												
Molecular markers^g^	*To be performed during the patient's participation in the study*															
Radiotherapy **(start max. 8 weeks since surgery and max. 2 weeks after planning MR)**		x														
Chemotherapy **(start max. 8 weeks since surgery and max. 2 weeks after planning MR)**		x	x	x	x	x	x	X	x	x	x	x	x	x		
Adverse events		x	x	x	x	x	x	X	x	x	x	x	x	x	x	x
PoF analysis^h^																x

The description of performed examinations:

^*^The pregnancy test will be performed at the center (1. As part of the screening phase before 11C-methionine applications and 2. Before the 1st application of concomitant chemoradiotherapy)

^**^Laboratory analysis incl. tests for HIV, HBV and HCV will be performed in the screening phase if they have not been performed in the previous 5 days

^***^Laboratory analysis (blood count + differential + biochemistry) will be performed every week as part of CHRT. Physical examination will be performed on D1 and D21 (if not performed in the previous 5 days)

^a^Anamnesis

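### Under the plan's own 8-month median, 67 patients give about 55 PFS events (up to about 63) at month 44, not the 65 stated, at a modest cost in power

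*Protocol article*

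**What the plan says.** All inputs are in the protocol article, mostly in Sample size {14}.

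- Comparator: "A historical retrospective cohort included 44 patients with REP who were indicated for adjuvant chemoradiotherapy (Arm Ahist".
- Its outcome, from the sentence that follows: "The median PFS in this cohort was 4.9 months".
- Error rates: "a significance level of 5%, and a power of 80" per cent. Sidedness is not given.
- Target: "65 events are needed to detect a hazard ratio of 1.65 (i.e., median PFS in the Experimental Arm of 8 months".
- Patients: "With an assumed recruitment of 38 months and a follow-up duration of six months, 67 patients are needed based on the historical cohort".
- Allowances: "With the expected screening failure rate of 5% and a dropout rate of 5%, approximately 75 patients with confirmed REP should be enrolled".

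Participant timeline {13} says: "The duration of the study participation is 44 months (recruitment 38 months + 6 months follow-up". Outcomes {12} measures PFS from the start of radiotherapy and gives the primary outcome a 44-month time frame. Study setting {9} dates the start of recruitment to October 2020 and adds: "Patient recruitment in the Czech Republic is planned to be completed in February 2024". The only distributional assumption in the sample size section is proportional hazards. Neither an event-time distribution nor an accrual pattern is stated.

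**The concern.** The 67 patients are derived from the 65 events, so 65 reads as the number required in the Experimental Arm, and 65/67 = 97% of its patients must have progressed or died by the cut-off. With entry spread over 38 months and a cut-off at month 44, follow-up ranges from 44 months for the first patient to 6 months for the last. If the median is 8 months, more than half of the latest entrants are expected to be event-free at that date. The event target, number of patients, accrual, follow-up and alternative therefore do not fit together.

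The trial is described as confirmatory and has no interim analysis. The event count determines how much information the single comparison carries. If the primary analysis is run at month 44 in the belief that 65 events will be there, the trial will report on fewer events than it declared, at a power that was never stated.

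**Working it through.** **Inputs from the protocol.** Accrual A = 38 months; follow-up after last entry F = 6 months; experimental median 8 months; historical median 4.9 months; 67 patients; 65 events; hazard ratio 1.65 (8/4.9 = 1.633).

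**Assumptions added here.** Exponential PFS and uniform accrual as the base case; Weibull shapes and uneven accrual as variations.

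**1. The plan's own figures.**
- 65 events: a 1:1 two-sided 5% design with 80% power needs 130.5 events in total by Freedman's formula at 1.65, or 130.7 by Schoenfeld's at 8/4.9. That is about 65 per arm, so the figure reproduces as a per-arm count.
- 75 enrolled: 67/(0.95 × 0.95) = 74.2, which reproduces.
- 67 patients, if everyone is followed for 44 months: 1 − exp(−44 ln2/8) = 0.978, and 65/0.978 = 66.5, so 67. This ignores staggered entry.
- 67 patients, from a historical curve with median 4.9 months and staggered entry: exponential PFS gives a probability of 0.921 and 61.7 events. A Weibull curve of shape 2 gives 65.6 events.

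**2. The stated design at the 8-month alternative.**

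P(event) = 1 − [exp(−λF) − exp(−λ(A+F))]/(λA), with λ = ln2/8 = 0.0866.

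P = 1 − (0.5946 − 0.0221)/3.292 = 0.826.

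- Expected events: 67 × 0.826 = 55.3.
- Patients for 65 events: 65/0.826 = 78.7, so 79 evaluable, or 79/0.9025 = 87.5, about 88 enrolled.
- Follow-up after last entry for 65 events from 67 patients: about 26 months.

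**3. Sensitivity, median 8 months, 67 patients unless noted.**

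| Variation | Expected events |
|---|---|
| Weibull shape 1.25 / 1.5 / 2 / 3 | 58.0 / 59.7 / 61.3 / 62.6 |
| Linearly front-loaded accrual, exponential | 60.8 |
| Linearly back-loaded accrual, exponential | 49.9 |
| Accrual 40–41 months (October 2020 to February 2024), 6 months' follow-up kept | about 56 |
| All 75 enrolled counted, no losses | 62.0 |
| Front-loaded accrual with Weibull shape 1.5 to 2 | 64.9 to 65.9 |

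Under uniform accrual there is also a ceiling for any distribution with an 8-month median. Patients entering in the last 2 of the 38 months are each at least 50% likely to be event-free, so the expected count cannot exceed 67 × (1 − 0.5 × 2/38) = 65.2. Reaching it would require half of the patients to have their event by month 6 and all the others immediately after month 8.

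**4. Effect on power.** Take all 44 historical patients as events (an assumption; the protocol gives patients, not events) and a hazard ratio of 1.65, so ln 1.65 = 0.501. The standard error of the log hazard ratio is √(1/d + 1/44), with d the events in the Experimental Arm.

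- d = 55.3: SE 0.202, ratio 2.479; power 69.8% two-sided, 79.8% one-sided.
- d = 65: SE 0.195, ratio 2.565; power 72.7% two-sided, 82.1% one-sided.

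**5. Later cut-off.** In the Stupp table, Visit 12 falls about 13.4 months after radiotherapy starts (42 days plus 12 months). With F = 13.4, the expected count is 60.9.

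**The case against.** The best defence is that the sentence names its basis: 67 is said to rest on the historical cohort. That cohort's curve is not shown, and if it is steep (Weibull shape about 2 around 4.9 months), 67 patients do give about 65 events. So 67 need not be an arithmetic slip. This stands as a possible explanation. It does not make the design consistent, because it uses the event rate expected without benefit, while power is defined at the 8-month alternative.

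It is also fair that 55 is the low end of the plausible event-time shapes under uniform accrual. Only proportional hazards is stated, steeper curves shrink the shortfall from about 10 events to 2–7, and front-loaded accrual combined with a steep curve closes it. The result is therefore best given as a range with its assumptions.

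Two stronger readings are tempting. A reader might infer that the shortfall by itself puts 80% power out of reach. It does not: one-sided, 55 events still give about 80%; two-sided, even 65 events give only about 73%, because the control group is fixed at 44 patients. That limit is a separate matter. A reader might also infer that a month-44 cut-off contradicts visit tables that run to progression. It does not: analysing before everyone has finished their visits is ordinary administrative censoring, and nothing says that visits stop at month 44.

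**Conclusion.** The point holds as a mismatch in the event count. Under the 8-month alternative, with 38 months' accrual and 6 months' follow-up, 67 evaluable patients give about 55 events at month 44 (exponential PFS, uniform accrual), or 58 to 63 for Weibull shapes 1.25 to 3, against 65 stated. The conclusion rests on reading 65 as Experimental Arm events, which the derivation of 67 implies, and on roughly uniform accrual. Reading 65 as the total over both groups would not rescue the plan: with 67:44 allocation, power at 1.65 would be about 51% two-sided or 63% one-sided.

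The cost in power is 2 to 3 percentage points on either sidedness, so this is a correction to a stated design figure and not a flaw that by itself defeats the trial.

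**What to change.** In Sample size {14}, state the event rate from which 67 was obtained, the expected Experimental Arm events at month 44 at the 8-month median (about 55, range 55 to 63, with the distribution and accrual assumed), and the power that follows, naming the test's sidedness. In Participant timeline {13}, describe 44 months as the length of the trial and not of each patient's participation. Both are wording changes; the cost is that the stated event count becomes less favourable.

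Optionally, set the primary cut-off at the last patient's Visit 12. This takes about 7 more months (13.4 − 6) and gives about 61 events, with no new patients or visits, but it still falls short of 65. If the sponsor prefers to wait for 65 events, the wait is about 20 months beyond month 44 (26 − 6) in the base case and should be costed as such.

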### Recruitment {15}

Recruitment of the patients has been carried out since October 2020. During the first four years, all planned patients will be recruited. The patients were recruited only at Masaryk Memorial Cancer Institute in Brno, Czech Republic.

The patient will be informed about the study during the visit, during which initial eligibility for the study will be determined, and the research staff will explain the study protocol and design.

## Methods: assignment of interventions: allocation

### Sequence generation {16a}, Concealment mechanism {16b}

The GlioMET study is nonrandomized, and the assignment of interventions is not applicable.

### Implementation {16c}

The study investigator will enroll the participants. All study visits will be scheduled to coincide with the regimen according to Stupp or Perry.

### Blinding (masking) {17a}

Not applicable. This study is not blinded; it is open-label.

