**Methods:**

This study is a nonrandomized, open-label, parallel-setting, prospective, monocentric clinical trial. The main aim of this study was to refine the diagnosis in patients with GBM with REP and to optimize subsequent radiotherapy planning.

Glioblastoma patients who develop REP within approximately 6 weeks after surgery will undergo ^11^C-methionine positron emission tomography (PET/CT) examinations. Target volumes for radiotherapy are defined using both standard planning T1-weighted contrast-enhanced MRI and PET/CT. The primary outcome is progression-free survival defined using RANO criteria and compared to a historical cohort with REP treated without PET/CT optimization of radiotherapy.

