### Outcomes {12}

Primary Outcome Measures of the clinical trial are to demonstrate the progression-free survival (PFS) in the 11C-methionine PET/CT arm as Experimental arm vs. PFS in the historical patient cohort as an arm Ahist. PFS was defined as the time from the start of radiotherapy to the progression of disease or death [Time Frame: 44 months].

The secondary outcomes are the following:

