Spatial evaluation of recurrence in relation to the area irradiated with a high dose of radiation (patterns of failure, PoF) is performed by a radiotherapist. MR defining progression according to RANO (MRRANO) criteria is used to analyze PoF, specifically T1-weighted sequence with contrast medium administration

Standard image fusion is performed in the radiotherapy planning system: MRRANO is registered to the original planning CT. The fusion is focused on the calf area (preferential choice of Hounsfield HU units in the bone band)

**Table 2 Tab2:** Participant timeline for the regimen according to Perry

4.3.2. Perry regimen	Screening	CHEMO RADIO THERAPY	Visit 1	Visit 2	Visit 3	Visit 4	Visit 5	Visit 6	Visit 7	Visit 8	Visit 9	Visit 10	Visit 11	Visit 12 (EoT)	Follow-up until PD	EoS Visit
Days / Months	**max. 14 D**	**D1-D21** **(M 1–2)**	**D21 + 1 M** (± 1 week)	** + 1 M**	** + 1 M**	** + 1 M**	** + 1 M**	** + 1 M**	** + 1 M**	** + 1 M**	** + 1 M**	** + 1 M**	** + 1 M**	** + 1 M**	**Every 3 M** (± 1 week)	**PD**
Inclusion/exclusion criteria	x															
Informed consent	x															
Anamnesis^a^	x															
Pregnancy test (serum/urine)	x*	x*	x	x	x	x	x	x	x	x	x	x	x			
HIV, HBV, HCV test	X**															
Physical and laboratory examination^b^	X**	x***	x	x	x	x	x	x	x	x	x	x	x	x		
ECOG Performance status	x	x	x	x	x	x	x	x	x	x	x	x	x	x		
Extent of surgery^c^	x															
^11^C-MET PET/CT^d^	x															
Quality of life questionnaires^e^	x			x		x		x		x		x		x	x	
MR and RANO evaluation^f^				x (á 3 months)												
Molecular markers^g^	*To be performed during the patient's participation in the study*															
Radiotherapy **(start max. 8 weeks since surgery and max. 2 weeks after planning MR)**		x														
Chemotherapy **(start max. 8 weeks since surgery and max. 2 weeks after planning MR)**		x	x	x	x	x	x	x	x	x	x	x	x	x		
Adverse events		x	x	x	x	x	x	x	x	x	x	x	x	x	x	x
PoF analysis^h^																x

The description of performed examinations:

^*^The pregnancy test will be performed at the center (1. As part of the screening phase before 11C-methionine applications and 2. Before the 1st application of concomitant chemoradiotherapy)

^**^Laboratory analysis incl. tests for HIV, HBV and HCV will be performed in the screening phase if they have not been performed in the previous 5 days

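### Section {17a} sets masking aside because treatment is open-label, though the progression date and the recurrence outline could still be read masked; the likely bias is modest and the main remedy nearly free

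*Protocol article*

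**What the plan says.** Blinding (masking) {17a} consists of one statement: "Not applicable. This study is not blinded; it is open-label". It gives the open-label design as the reason and does not distinguish masking of treatment from masking of image readers.

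Two image-based outcomes are compared between arms.

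- **Primary, PFS.** The Abstract states: "The primary outcome is progression-free survival defined using RANO criteria and compared to a historical cohort with REP treated without PET/CT optimization of radiotherapy". Outcomes {12} adds: "PFS was defined as the time from the start of radiotherapy to the progression of disease or death". The tables in Participant timeline {13} schedule MR with RANO evaluation every 3 months.
- **Secondary, PoF.** Outcomes {12} classes each recurrence by V95%, with cut-points at 20%, 80% and 95%, and compares the Experimental Arm with Arm Ahist. Footnote h of the tables in {13} says: "Spatial evaluation of recurrence in relation to the area irradiated with a high dose of radiation (patterns of failure, PoF) is performed by a radiotherapist". It continues: "Standard image fusion is performed in the radiotherapy planning system: MRRANO is registered to the original planning CT".

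On the comparator, Study setting {9} says: "The control cohort consisted of a historical group of patients collected in the period 2014–2018". Trial recruitment began in October 2020. Sample size {14} gives 44 historical patients and a median PFS of 4.9 months, so the benchmark was known before the trial. Trial design {8} calls the comparison confirmatory.

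**The concern.** The inference in {17a} does not follow. Open-label means that patients and treating staff know what was given. It does not stop a reader from assessing a stored MR without the arm label, the date or the dose plan.

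Both outcomes involve judgement. The RANO date depends on whether a change at one scan is called progression or is left to the next scan. V95% depends on where the recurrence edge is drawn relative to the high-dose region. Three features of the article leave room for knowledge to influence these calls:

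- no masked reading is stated;
- the arms come from separate calendar periods, so an undisguised scan date reveals the arm;
- PoF is done in the planning system on the planning CT, where dose and target structures can be displayed.

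If trial progressions were called late while the historical dates stayed as they were, the primary comparison would move towards PET. Covariate adjustment cannot correct a shifted outcome date.

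**Working it through.** **1. Inputs.** From Sample size {14}: 44 historical patients, median 4.9 months, 65 events, 67 trial patients, hazard ratio 1.65 (8 vs 4.9 months), 5% significance level, 80% power, 38 months of recruitment and 6 of follow-up. From {13}: a 3-month MR interval. From {12}: the V95% cut-points. Assumed: all 44 historical patients had an event (the number is not stated), exponential times, and the rates of late calling.

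**2. The plan's own figure.** Against a fixed historical arm, SE(log HR) = √(1/65 + 1/44) = 0.195.

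- One-sided 5%: power = Φ(ln(8/4.9)/0.195 − 1.645) = 80.7%, or 82.1% with HR 1.65. The plan's 80% is reproduced.
- Two-sided 5%: 71–73%.

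**3. Gain needed for significance.** Two-sided, the critical HR is exp(1.96 × 0.195) = 1.47. On the 4.9-month benchmark this is 4.9 × 1.466 = 7.2 months, a gain of 2.3 months. That is shorter than one MR interval, so the timing of a call is not a negligible quantity.

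**4. PFS with no true effect.** Simulation settings: median 4.9 months in both arms, 67 vs 44 patients, trial censoring uniform over 6–44 months, two-sided 5% log-rank test. The table counts significant results in favour of PET (nominally 2.5%).

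| Trial progressions called one 3-month scan late | Favourable false positives, repeated runs | On a 3-month scan grid, 20% of events deaths that cannot shift | Average HR |
|---|---|---|---|
| 0% | 2.6–3.0% | 2.9% | – |
| 10% | 4.4–5.1% | 4.0% | 0.94 |
| 20% | 7.2–7.6% | 7.0% | 0.90 |
| 30% | 10.5–11.5% | 9.4% | 0.86 |

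For scale, the design effect is 1/1.65 = 0.61. Moving every trial progression later by 0.5 month gives about 6%, and by 1 month about 12–13%.

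**5. PoF.** Assume a spherical recurrence of radius r cut by a flat 95% isodose edge. The covered fraction is V95% = h²(3r − h)/(4r³), where h is the depth of the covered cap. Solve for h at each cut-point, then change h by 1 mm.

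| Starting V95% | 2 cm lesion (r = 10 mm), ±1 mm | 4 cm lesion (r = 20 mm), ±1 mm |
|---|---|---|
| 20% | +6.4 / −5.8 points | +3.1 / −3.0 points |
| 80% | +5.8 / −6.4 points | +3.0 / −3.1 points |
| 95% | +2.9 / −4.0 points | +1.6 / −1.9 points |

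Worked case, 2 cm lesion at 79%: h = 14.10 mm. With h = 15.10 mm, V95% is 84.9%, and the class changes from marginal to in-field. For a 4 cm lesion the same 1 mm takes 79% to 82.0%, also across the limit. The sensitivity halves when the diameter doubles, so only lesions close to a cut-point are affected.

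**The case against.** Several points against the concern stand.

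- **The readers and the workflow are not described.** The article does not name who assigns the RANO date, and for PoF it says only that the evaluation "is performed by a radiotherapist". It does not give the order of contouring and dose display. A reader might infer that the trial team is known to read with arm and dose in view. The documents support only that this may happen. Such detail could sit in the full protocol, which is not shown. The entry in {17a} is nevertheless a positive statement rather than a silence.
- **Each modelled PFS shift is large.** A whole scan is 3/4.9 = 61% of the benchmark median. Even with 30% of progressions delayed, about 89% of null trials still show no significant benefit. Deaths count as PFS events and cannot be moved by reading. Nothing in the article indicates a delay rate or its direction. A reader might infer that small shifts can create a PET benefit by themselves; the figures do not show this.
- **One-sided bias is not shown for PoF.** One PoF method is described and no separate one is given for Ahist, so visible dose could influence both arms. The article also does not say how many lesions lie near a cut-point.
- **Masked dates would be unsafe as the primary dates.** Scheduled scans stop at progression. A masked reader can move a date earlier, but often cannot move it later, and an unconfirmed progression would be censored informatively. Storage of all Ahist MRs is not documented either.

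These points limit the size of the concern and the form of the remedy. They do not rescue the inference that open-label treatment makes masking inapplicable.

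**Conclusion.** The point holds in a limited form. The reason given in {17a} is wrong, and as described both image-based comparisons may be read with arm and dose known.

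For PFS the possible inflation is modest: from about 3% to about 5/7/10–11% when 10/20/30% of trial progressions are called one scan late, and about 4/7/9% with 20% of events being deaths. This rests on assumed delay rates, exponential times, events in all 44 historical patients, and historical dates left as they are. It mainly matters for a borderline result. For PoF, a 1 mm contour difference is enough to reclassify lesions near a limit: about 6 points at the 20% and 80% limits for a 2 cm lesion and about 3 for a 4 cm lesion, under the spherical, flat-edge assumption.

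Masked reading would not remove the other weaknesses of a historical control. The case for change rests mainly on how little the PoF step costs.

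**What to change.** Replace the entry in {17a} with two provisions.

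1. **PoF, both arms.** Outline the recurrence on the progression MR with dose, target and PET structures hidden. Lock the contour, and only then overlay the dose and compute V95%. This changes only the order of steps.
2. **PFS, as a sensitivity analysis.** Re-read the available stored MRs of trial and Ahist patients in one mixed series, with arm label, calendar date and PET removed. Keep the existing progression dates for the primary analysis. Report how many progressions are not confirmed in each arm and how they are handled, because scheduled scans stop at progression. Report also how many Ahist patients had no readable MR.

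No extra patient, scan or change of treatment is needed. The cost is reading time and retrieval of stored scans. Some Ahist scans may be unavailable, and differences in image quality between the periods may partly reveal the arm.
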